### Blinding

Due to the nature of the study, the participants are blinded to the intervention.

## Data collection, management, and analysis

### Data management

Data will be collected with paper data collection forms and entered into a Microsoft Excel sheet within 48 hours of data collection. At the end of the study the Excel sheet will be rechecked against the paper originals and any inconsistencies will be noted and discussed between the PI and Research Technician in charge of data entry.

### Statistical plan

Data will be analyzed with a repeated measures ANOVA test and Sidak *post hoc* testing using SPSS version 28.0. We will examine both group-by-sex and group-by-age interactions, and report effect sizes along with confidence intervals, in addition to p-values. All tests will be two-sided with alpha set at 0.05.

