### Power analysis and sample size

A minimum of 16 and a maximum of 24 participants will be enrolled and randomized into groups. To our knowledge, the effect of IMST on fasting glucose and/or insulin sensitivity in any population have not previously been reported, nor have effects of IMST on systolic BP and EDD in T2DM been specifically ascertained. Thus, for our power analysis we estimated a modest effect size of 0.40 with alpha set at 0.05 using a repeated measures ANOVA within-between framework. A sample size of 16-24 will have 85-96% power for any outcome with an effect size of ≥ 0.40.

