## Assignment of interventions

### Sequence generation

The randomization sequence will be created using computer-generated random numbers at a 1:1 ratio in blocks of four. Male and female participants will be randomized using separate randomization tables.

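### The planned pre-post ANOVA is valid, but adjusting for baseline would estimate the treatment effect more precisely at almost no cost if the pre-post correlation is low to moderate

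*Protocol article*

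**What the plan says.** The Statistical plan gives the method in one sentence: "Data will be analyzed with a repeated measures ANOVA test and Sidak" post hoc tests. It adds "We will examine both group-by-sex and group-by-age interactions" and "All tests will be two-sided with alpha set at 0.05". It names no baseline covariate and no sex term for the main comparison.

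Under Sequence generation, allocation uses "computer-generated random numbers at a 1:1 ratio in blocks of four", and "Male and female participants will be randomized using separate randomization tables", so sex is a randomisation stratum.

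Power analysis and sample size gives "A minimum of 16 and a maximum of 24 participants will be enrolled and randomized into groups". For power, "we estimated a modest effect size of 0.40 with alpha set at 0.05 using a repeated measures ANOVA within-between framework", with the result "A sample size of 16-24 will have 85-96% power for any outcome with an effect size of ≥ 0.40".

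The Outcomes section takes fasting glucose and insulin (and so HOMA-IR) at the baseline and post-intervention visits, and resting blood pressure before and after the intervention. Table 2 also places flow-mediated dilation once before and once after training. Weekly blood pressure checks, and the glucose checks around supervised sessions (called exploratory), do not change these outcome definitions.

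**The concern.** A trial of 16 to 24 people has little precision to spare. With two time points, the planned analysis subtracts the whole baseline value from the end value. Unless the two values are very highly correlated, that subtracts too much and adds the noise of the baseline measurement to the comparison. A model that estimates the baseline slope from the data avoids this and needs no extra data.

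A smaller point concerns wording. Taken literally, a group-by-sex term in a repeated measures ANOVA compares participants on the average of their pre and post values. Whether training works differently in men and women is a question about change. The wording should make clear which is meant.

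**Working it through.** **Inputs.** From the article: total N of 16 to 24, 1:1 (8 to 12 per arm); effect size 0.40; two-sided alpha 0.05; two measurements per outcome. Assumptions: 0.40 is Cohen's f; SD equal at both times; no dropout; pre-post correlation ρ = 0.5, with 0.3 to 0.9 shown. Effects are in units of the SD of a single measurement.

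**1. Reproduce the stated power.** For group-by-time with two groups and two times, λ = f²·N·2/(1−ρ) on 1 and N−2 df.
- N=16: 0.16 × 16 × 2 / 0.5 = 10.24, power 84.5%.
- N=24: 0.16 × 24 × 2 / 0.5 = 15.36, power 96.3%.

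These match 85% and 96%. Other inputs do not: ρ = 0.3 gives 71.1% and 88.6%, ρ = 0.7 gives 97.0% and 99.8%, and the between-group main effect gives 40.6% and 58.1%. The trial was therefore powered on the difference in change. In terms of a between-arm difference δ in change, λ = δ²N/(8(1−ρ)), so δ = 4f = 1.6 SD.

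**2. Compare the error variances.** The change score has variance 2(1−ρ); ANCOVA has residual variance 1−ρ². The ratio is (1+ρ)/2 = 0.75 at ρ = 0.5. Estimating the slope costs a factor (N−3)/(N−4):
- N=16: 0.75 × 13/12 = 0.81.
- N=24: 0.75 × 21/20 = 0.79.

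The same point in terms of imbalance: the difference in baseline means has SD √(4/N) = 0.50 (N=16) or 0.41 (N=24). The change-score estimate carries −(1−ρ) times that difference, which is half of it at ρ = 0.5. Over repeated randomisations this averages to zero, so it is noise and not bias.

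**3. Confidence interval half-widths at ρ = 0.5.**
- Planned test, t(N−2)·√(2(1−ρ)·4/N): 1.072 SD and 0.847 SD for N=16 and 24.
- Baseline adjusted, t(N−3)·√((1−ρ²)·4/N·(N−3)/(N−4)): 0.974 and 0.753, narrower by 9% and 11%.
- Baseline and sex, t(N−4)·√((1−ρ²)·4/N·(N−4)/(N−5)): 0.985 and 0.757, narrower by 8% and 11%.

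Simulated mean half-widths with both covariates (8,000 runs per setting) fell from 1.052 to 0.962 (9%) and from 0.839 to 0.749 (11%).

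**4. Range of ρ.** Planned test → model with baseline and sex:

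| ρ | N | CI half-width (SD) | Power, 1.0 SD (%) | Power, 1.6 SD (%) |
|---|---|---|---|---|
| 0.3 | 16 | 1.269 → 1.085 | 35.0 → 46.1 | 71.1 → 84.2 |
| 0.3 | 24 | 1.002 → 0.833 | 50.8 → 66.6 | 88.6 → 96.7 |
| 0.5 | 16 | 1.072 → 0.985 | 46.1 → 53.6 | 84.5 → 90.2 |
| 0.5 | 24 | 0.847 → 0.757 | 64.9 → 74.8 | 96.3 → 98.7 |
| 0.7 | 16 | 0.831 → 0.813 | 67.1 → 69.8 | 97.0 → 97.5 |
| 0.7 | 24 | 0.656 → 0.624 | 85.6 → 88.9 | 99.8 → 99.9 |
| 0.8 | 16 | 0.678 → 0.683 | 83.6 → 83.7 | 99.7 → 99.6 |
| 0.8 | 24 | 0.535 → 0.524 | 95.9 → 96.5 | 100 → 100 |
| 0.9 | 16 | 0.480 → 0.496 | 98.6 → 98.0 | 100 → 100 |
| 0.9 | 24 | 0.379 → 0.381 | 99.9 → 99.9 | 100 → 100 |

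Simulation at ρ = 0.5 and 1.0 SD gave 46% → 54% and 65% → 74%.

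**5. Sex on its own** (5,000 simulated runs per setting, ρ = 0.5, 1.0 SD effect, change-score test). A sex effect that is equal at both times cancels: power at N=16 was 47% without sex and 46% with it. With a sex-by-time effect of 0.5 SD, omitting sex gave 44% against 47% (N=16) and 61% against 63% (N=24), with type I error of 4.2% and 4.3%. Sex therefore adds little precision; the gain in step 4 comes from baseline.

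**6. The interaction term.** Take an effect modification of 1.6 SD, ρ = 0.5 and N/4 people per cell. Literal group-by-sex carries half of it: λ = 0.8²/(0.75 × 16/N), power 14% (N=16) and 19% (N=24). Group-by-sex-by-time has λ = 1.6²/(1 × 16/N), power 31% and 46%.

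**The case against.** The planned test is standard, matches the framework used for sizing, and is valid in a trial that calls itself exploratory. All of that stands. Four stronger readings might be inferred, and the article does not support them.

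- *Baseline is ignored.* It is not: it is one of the two repeated measures, used with its slope fixed at 1.
- *The estimate is biased by baseline imbalance.* Under randomisation it is unbiased. Imbalance shifts a particular estimate and adds variance.
- *Leaving out the sex stratum costs power.* Step 5 shows a loss of nothing to 2-3 points. The planned group-by-sex check also implies that sex enters at least one model.
- *The group-by-sex term tests the wrong thing.* That holds only if a short phrase is read literally. The power calculation concerns the difference in change, so the phrase may well be shorthand for modification of that difference. In either case it does not affect the precision of the treatment comparison.

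A further objection is that ρ = 0.5 is worked back from the power statement. It shows what the planners probably assumed, not how glucose, insulin, HOMA-IR, blood pressure or flow-mediated dilation will behave over six weeks. This also stands, so the gain has to be given as a range. What remains is that the article names a specific method, and a more precise one is available from the same data.

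**Conclusion.** This is a nearly free improvement, not an error of validity. At ρ = 0.5 the gain is useful: roughly a tenth off the interval width, about 6 points of power at N=16 for the plan's own effect (2 to 3 at N=24), and 7 to 10 points for a 1.0 SD effect. It is larger at ρ = 0.3, small at 0.7 and about nil at 0.8. The worst case shown is an interval about 3% wider, at N=16 and ρ = 0.9. These sizes rest on the unstated correlation, the Cohen's f reading of 0.40, equal variances at both times and no dropout. The interaction wording is an ambiguity to clear up.

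**What to change.** Replace the main analysis sentence with one model per outcome: a linear regression of the end-intervention value on arm, the baseline value of that outcome, and sex. Report the arm coefficient with its 95% confidence interval as the treatment effect. Sex is included so that the analysis matches the stratified randomisation, not for the precision it adds.

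State the effect-modification checks as arm-by-sex and arm-by-age terms added to this model. They serve the same purpose as group-by-time-by-sex and group-by-time-by-age in the ANOVA. Label them descriptive: with equal numbers of men and women there are only 4 to 6 people per arm-by-sex cell (16/4 to 24/4).

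The cost is one paragraph of text and two residual degrees of freedom in the main model (N−4 in place of N−2). It needs no new data and runs in the software already named.

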### Participant timeline

The timeline for participation in the study will be 7-9 weeks as shown in **Figure 1**. A summary of the visits for the DIT study participants is shown in **Table 2**.

**Table 2 T2:** Summary of the visits for the DIT study.

	Baseline		Training	End-Intervention	
	Visit 1	Visit 2	Week 1-6	Visit 1	Visit 2
Screening					
Informed Consent	X				
Demographics	X				
Medical History	X				
Inclusion/Exclusion	X				
Hip/waist/neck circumference	X			X	
Functional Assessments					
Resting BP	X		X	X	
PI_max_	X		X	X	
Spirometry	X			X	
Blood Draw					
Metabolic panel		X			X
Plasma/DNA		X			X
Arterial Assessments					
FMD_BA_	X			X	
At-home Testing					
Sleep/exercise diary			X		
Exercise sessions					
Daily exercise			X		
Once-weekly supervised exercise session*			X		
Weekly text/email			X		
Randomization		X			

BP, Blood Pressure; FMD_BA_, Flow-mediated dilation of brachial artery; PI_max_, Maximal inspiratory mouth pressure. *, At this weekly supervised training session, the participant will do a fasting plasma glucose check immediately before and after the training session.

Participants will sign a written informed consent with a member of the research team at the CATS facility. Following informed consent, participants will complete all baseline assessments in two in-person visits to the CATS facility within a 14-day window. Participants will begin the 6-week intervention ≤ 14 days after baseline assessments are completed. If the participant is unable to make one of their in-person training sessions, they will proceed to do their exercises at home and come the following week for their regularly scheduled training session in order to maintain the 6-week training regimen. During the weekly training session at the CATS facility, a weekly blood pressure check will be performed (41). In addition, during the weekly visit, plasma glucose levels will be measured immediately before and after the exercise session. These measurements are exploratory and aim to identify any immediate effects of IMST on plasma glucose levels. All assessments will be repeated within 14 days after completion of the 6-week training program. Participants will continue to perform IMST 5 days/week until all post assessments are completed.

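### The only named analysis, repeated measures ANOVA, would drop any participant with one missed weekly visit if applied across the six weeks of exploratory before/after-session glucose

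*Protocol article*

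**What the plan says.** The Statistical plan section of the protocol article reads "Data will be analyzed with a repeated measures ANOVA test", with Sidak post hoc tests in SPSS 28.0, and adds "All tests will be two-sided with alpha set at 0.05". No other model is named, and the sentence is not limited to particular outcomes.

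The Participant timeline section says that at the weekly visit "plasma glucose levels will be measured immediately before and after the exercise session". It calls these values exploratory and gives their purpose as finding immediate effects of the training. With one supervised session a week for six weeks (Interventions section), that is up to 6 × 2 = 12 values per person. Table 2 also lists resting blood pressure and PImax during weeks 1-6.

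The same section covers absences: "If the participant is unable to make one of their in-person training sessions, they will proceed to do their exercises at home". The participant then returns at the next scheduled week, so the missed week's pair of glucose values is neither taken nor replaced.

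The primary glucose and insulin samples are drawn at baseline and post-intervention only (Primary outcomes section). On size, the article says "A minimum of 16 and a maximum of 24 participants will be enrolled and randomized into groups".

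**The concern.** The usual SPSS repeated-measures procedure takes one row per participant and excludes the whole row if any within-subject value is missing. Applied with week as a within-subject factor, it conflicts with the article's own visit rule. A participant who completes the trial but misses one weekly visit, as the protocol permits, would lose up to ten valid glucose values along with the two that were never taken.

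With 16 to 24 participants, even a few such exclusions matter. The acute-effect question would be answered only in people with perfect weekly attendance. That costs precision in every case. It would also weaken the randomised comparison if attendance were related to arm or to glucose, which the article neither says nor rules out.

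**Working it through.** **1. What the stated power was computed for.** Inputs from the Power analysis section: "we estimated a modest effect size of 0.40", alpha 0.05, "using a repeated measures ANOVA within-between framework". The metric and the within-person correlation are not given; I take Cohen's f and assume a correlation ρ = 0.5. For k = 2 groups and m = 2 time points:

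λ = f²·N·m/(1−ρ), with 1 and N−2 degrees of freedom.

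- N = 16: λ = 0.16 × 16 × 2/0.5 = 10.24, power 84.5%
- N = 24: λ = 0.16 × 24 × 2/0.5 = 15.36, power 96.3%

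This reproduces "A sample size of 16-24 will have 85-96% power for any outcome with an effect size of ≥ 0.40". On these assumptions the calculation describes a pre/post design, not a six-week series.

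**2. Complete rows over six visits.** The article gives no missed-visit rate, so the rate q is an assumption, with misses taken as independent and equally likely at each visit. The expected share with all six visits is (1−q)⁶.

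| q per visit | complete share | of 16 | of 24 |
|---|---|---|---|
| 2% | 88.6% | 14.2 | 21.3 |
| 5% | 73.5% | 11.8 | 17.6 |
| 10% | 53.1% | 8.5 | 12.8 |

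Of the sessions actually attended, the share discarded is 1−(1−q)⁵, because an attended session is kept only if the other five are attended too: 9.6%, 22.6% and 41.0% respectively.

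**3. Effect on precision.** Take the after-minus-before change at each session as the outcome, with between-person SD τ and within-person SD σ. Compare 95% confidence interval half-widths for the arm difference:

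- complete rows only, n_c = N(1−q)⁶: t(n_c−2) × √[4(τ² + σ²/6)/n_c]
- all attended sessions: t(N−2) × √[4/info], where info = N × Σ P(k attended)/(τ² + σ²/k), summed over k = 1 to 6 with binomial probabilities

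Worked case, q = 5%, N = 24, τ = 0, σ = 1:

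- complete rows: 2.124 × √[4 × (1/6)/17.64] = 0.413
- all attended sessions: info = 136.8, so 2.074 × √(4/136.8) = 0.355
- ratio 1.16

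With τ/σ from 0 to 1, the interval from complete rows is wider by:

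| q per visit | N = 24 | N = 16 |
|---|---|---|
| 2% | 6-7% | 7-8% |
| 5% | 16-19% | 19-21% |
| 10% | 38-45% | 46-52% |

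These are approximations: the expected number of complete rows is used as if it were the achieved number.

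**4. Where the loss does not arise.** If the analysis uses a two-level before/after factor on each participant's average session, everyone with at least one attended visit stays in and almost nobody is lost. The pre/post outcomes do not use the weekly visits at all.

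**The case against.** The strongest reply is that the Statistical plan never says the weekly glucose enters an ANOVA with a six-level week factor. The power statement reproduces as a two-time-point design and the main outcomes are measured pre and post, so the sentence can be read as the pre/post analysis only. The weekly glucose is labelled exploratory, appears under the Participant timeline rather than among the listed outcomes, and may be covered in a fuller protocol or analysis plan that is not shown.

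Much of this stands. It makes the point conditional and minor. It does not remove it: the article does state a method, states it for the data without limit, and pairs it with a visit rule that produces incomplete rows. The point is a poor fit between two stated things, not a missing detail.

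A reader might infer stronger conclusions that the article does not support:

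- **That the loss is large.** The rule on missed sessions is a contingency with no rate attached. At 2% missed, the interval widens by only 6-8%.
- **That the loss is non-random.** No reasons for absence are given, nor any link to arm or glucose. Under the independent misses assumed above, complete rows are a random subset: precision falls, but no bias follows.
- **That the analysis becomes barely estimable.** The acute-effect contrast between arms, averaged over weeks, has one degree of freedom and needs no sphericity correction.
- **That the weekly blood pressure and PImax series are affected.** This holds only if they are analysed. PImax is taken weekly to reset the training resistance, and no analysis of either weekly series is stated.

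**Conclusion.** The point holds in conditional form and is minor. If the weekly before/after glucose is analysed across all six weeks by the only method named, each participant with one missed visit is excluded, at the cost in precision tabulated above. Those figures rest on three assumptions outside the article: the miss rate, independent misses at a common rate, and a between- to within-person SD ratio of 0 to 1. They also assume the one-row-per-participant form of the ANOVA with week as a factor.

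The consequence is confined to the exploratory question of immediate effects on glucose. No primary or secondary result changes, because fasting glucose, insulin, HOMA-IR, resting blood pressure and endothelium-dependent dilation are compared pre to post.

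**What to change.** In the Statistical plan, limit repeated measures ANOVA to the pre/post outcomes and name one of two analyses for the weekly glucose:

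- **Linear mixed model (SPSS MIXED).** The outcome is the after-minus-before change at each attended session. Arm and week are fixed effects, with a random intercept for participant, fitted by REML with Kenward-Roger or Satterthwaite degrees of freedom. The arm difference is the acute effect.
- **Per-participant summary.** Compare arms on each participant's mean change over attended sessions.

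Either keeps everyone with at least one attended session. Do not adjust for each week's pre-session glucose: it is measured after randomisation and may itself be changed by training, since lowering fasting glucose is the primary hypothesis. Baseline fasting glucose may be used as a covariate instead. If weekly blood pressure or PImax is to be analysed, a mixed model of the same form, on the weekly value, would serve.

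The cost is a sentence or two in the plan and a different procedure in the same package. No new data, visits or participants are needed.

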## Monitoring

### Data monitoring

The intervention is low-risk and does not require a data monitoring committee. The research team will meet with the study physician at regular intervals to track study progress and discuss any potential safety issues. No interim analyses will be performed.

### Harms

An adverse event (AE) is any harmful and unintended reaction during the course of the study that may be related or unrelated to the intervention. All AEs occurring between a participant signing the informed consent and completing post-intervention assessments will be reported to the study physician.

## Anticipated results

### Primary hypothesis

Six weeks of high-resistance IMST will lower fasting plasma glucose and improve insulin sensitivity.

### Other hypotheses

Six weeks of high-resistance IMST will:

Lower resting systolic BPImprove EDD

## Discussion

Regular exercise is one of the most commonly prescribed non-pharmacological interventions for T2DM management and yields improvements in glycemic control and insulin action (6, 7). However, aerobic exercise is physically strenuous and time-consuming (10, 11) and less than half of T2DM adults participate in exercise on a regular basis. IIn contrast, IMST is a novel form of high intensity training that can be performed whether sitting or standing requires only 5 minutes per day, and rapidly improves blood pressure, endothelial vascular function, and vascular resistance among hypertensive adults (17, 18, 20, 28). Whether IMST can also affect changes in fasting blood glucose or insulin sensitivity is of critical interest and important for adults with T2DM, along with establishing if these blood pressure lowering effects and increased EDD are also seen in this population following IMST.

A study by Corrêa et al. studied the acute effects of IMST on glucose variability and showed significant improvements in glucose immediately following the training (42). Additionally, another study which was for 12 weeks at a lower resistance of 30% revealed no significant changes in blood glucose levels (43). The discrepancies across these findings are likely due to populations studied, the timeframe of the training and the resistance used. To our knowledge there have been no investigations that have reported the effects of chronic IMST training at a resistance of 75% or an interval training protocol similar to ours on glycemic control and insulin sensitivity in T2DM.

We expect the IMST intervention to enhance vascular health, as well as improvements in metabolic health. We propose that IMST may enhance insulin sensitivity and endothelial function by increasing NO bioavailability and reducing oxidative stress (**Figure 2**). Previous research by Bailey et al. demonstrated that endothelial function and NO bioavailability improved after six weeks of high-resistance IMST in older adults with normal to elevated blood pressure (18). This suggests that IMST enhances endothelial function by activating endothelial nitric oxide synthase (eNOS), which likely increases NO levels essential for vasodilation and improved blood flow (18). This mechanism reduces ROS, maintains NO levels, and supports vascular health. The increased NO not only improves endothelial function but also enhances glucose uptake by improving blood flow to skeletal muscles (23), potentially boosting insulin sensitivity. We hypothesize that these pathways activated by IMST could improve cardiometabolic health, particularly in individuals with T2DM.

